## Abstract

**Background:**

Arterial hypertension is a major risk factor for cardiovascular disease and leads to target organ damage including stroke, heart failure, and kidney disease. About 1.5 billion people worldwide have hypertension, and it is estimated that it causes about 8 million deaths each year. Although there are several drugs available to lower blood pressure (BP), a great proportion of treated patients does not reach recommended treatment targets. Typical antihypertensive drugs target the vessels, the kidneys, and the heart. However, our gut microbiota also influences cardiovascular health, and gut dysbiosis is associated with hypertension. In this study protocol, we investigate the potential BP-lowering effect of a probiotic in patients with grade 1 hypertension.

**Methods:**

This study is an exploratory, randomized, double-blind, placebo-controlled, parallel-group study. One hundred ten patients with grade 1 hypertension (treated or untreated) will be randomized to either the probiotic Vivomixx® or placebo. The primary endpoint is the nocturnal systolic BP measured by ambulatory blood pressure monitoring after 8 weeks adjusted for the baseline value. The secondary endpoints are changes from baseline in nocturnal diastolic BP, antihypertensive medication, fecal microbiome composition, fecal and serum metabolome, immune cell phenotypes, glucose variability after three standardized breakfasts, and health-related quality of life (PROMIS-29). We also assess the safety profile of the intervention.

**Discussion:**

We postulate that various administrated bacteria (*Lactobacilli*, *Bifidobacteria*, and *Streptococcus thermophilus*) convert dietary components into active metabolites that positively affect immune cell function. A reduction of pro-inflammatory immune cell function could promote a BP-lowering effect.

**Trial registration:**

ClinicalTrials.gov NCT03906578. Registered on 08 April 2019

**Supplementary Information:**

The online version contains supplementary material available at 10.1186/s13063-020-04973-0.

## Introduction

Arterial hypertension is one of the major risk factors for cardiovascular disease, including ischemic heart disease, heart failure, kidney disease, and stroke. About 1.5 billion people worldwide develop arterial hypertension [1] to which about 8 million premature deaths per year are attributable [2]. The Global Burden of Disease Study 2013 revealed that—after dietary risks—high systolic blood pressure (BP) was the second most important risk factor for morbidity and mortality globally, exceeding the risks of tobacco smoke, high body mass index, high fasting plasma glucose, and high total cholesterol [3]. In 2017, 15% of women and 25% of men in Germany had elevated BP [4].

Commonly used antihypertensive drugs typically target different hormone systems (e.g., renin-angiotensin system) and the production of endogenous vasoactive substances, aiming to protect the blood vessels, heart, and kidney. However, despite the fact that there are several drugs available to lower BP, a large proportion of treated patients do not reach the BP targets recommended by current guidelines [5]. Non-pharmacological approaches to prevent and treat hypertension are lifestyle modifications, such as increased physical activity, reduced salt and alcohol intake, weight loss, and a healthy diet [6].

Another non-pharmacological approach to lower BP is the use of probiotics. Research efforts in this field first focused on milk fermented with *Lactobacillus helveticus*, which contains two tripeptides that inhibit the angiotensin-converting enzyme [7]. Since 1996, a number of clinical studies that investigated the BP-lowering effects of fermented dairy products in hypertensive subjects were published, and the majority of them showed BP-lowering effects. However, a Cochrane review in 2012 evaluated these studies and concluded that the effect on systolic BP was too modest to recommend a general use in the treatment of hypertension [8]. Two years later, a meta-analysis of 9 studies, which investigated the effect of various probiotics, found a modest but clinically meaningful BP reduction [9]. This was confirmed by a very recent meta-analysis of 14 studies published between 2002 and 2019 [10].

Here, we use a probiotic formulation with a high concentration of eight different live bacterial strains. Our proposed mode of action is not through angiotensin-converting enzyme inhibition but through the modulation of the microbiota-immune interaction. The gut microbiota is thought to be relevant for cardiovascular health [11], and microbial imbalance is linked to experimental and human hypertension [12, 13]. This is supported by recent epidemiological evidence showing that higher total yogurt intake lowers the risk of incident high BP in middle-aged and older adults [14]. Furthermore, hypertensive subjects with a high yogurt intake had a lower risk of developing cardiovascular disease [15].

Microbial metabolites are resorbed from the intestinal lumen and affect various functions of the host. Their effects are not restricted to the intestine but also affect the immune system, the vasculature, and the kidney. Hypertensive organ damage seems to be largely mediated by immune cells like effector memory T cells [16] and T cells producing interleukin-17 (Th17 cells) [17]. Recently, we demonstrated that a high-salt diet affected fecal *Lactobacillus* abundance in mice and humans alongside increased BP and Th17 abundance. A probiotic *Lactobacillus* treatment reduced the salt-induced increase in BP and Th17 [18]. In an exploratory study, we found that Vivomixx® prevented a high salt-induced increase in BP in healthy men (unpublished data, NCT02971787). In subjects eating a synbiotic yogurt for 90 days, we found that an increased capacity for intestinal short-chain fatty acid production was correlated with diastolic BP reduction [19].

Here, we present the protocol of a randomized, double-blind, placebo-controlled study investigating the effects of a probiotic in patients with grade 1 hypertension. We hypothesize that the probiotic is superior to placebo in lowering BP. Secondary endpoints are changes in antihypertensive medication, fecal microbiome composition, fecal and serum metabolome, immune cell phenotypes, glucose variability after three standardized breakfasts, and health-related quality of life.

## Methods

### Study design

This is an exploratory, randomized, double-blind, placebo-controlled, parallel-group study conducted at the Experimental and Clinical Research Center of Charité - Universitätsmedizin Berlin, Germany. Recruitment started in August 2019 (ClinicalTrials.gov identifier: NCT03906578). Patients are recruited from greater Berlin, Germany. Recruitment is performed via the hypertension outpatient clinic at Helios Klinikum Berlin-Buch, study flyers in medical practices, and advertisements in a broad range of media relevant to the study population. We intend to randomize 110 patients with grade 1 hypertension to either 8 weeks of Vivomixx® or placebo. The intervention is followed by a 4-week recovery period.

This study protocol was approved by the institutional review board of Charité - Universitätsmedizin Berlin, and we obtain written informed consent from all participants before study entry (Additional files 1 and 2). The study is conducted in accordance with the Declaration of Helsinki in its currently applicable version, the guidelines of the International Conference on Harmonization of Good Clinical Practice (ICH-GCP), and applicable German laws.

### Participants

Information and informed consent forms have been prepared in accordance with the guidelines of the institutional review board of Charité - Universitätsmedizin Berlin. Potential participants receive both forms at least 1 day before their screening visit. During this visit, a study physician explains all study procedures, and written informed consent is only given after participants had adequate time to ask questions. We include men and postmenopausal women with grade 1 hypertension in this study.

### Complete list of inclusion criteria

Men and postmenopausal women (ratio 1:1)50–75 years of ageGrade 1 hypertension, defined as resting office blood pressure of 140–159 and/or 90–99 mmHg according to the European Societies of Cardiology and Hypertension (ESC/ESH) guidelines [20]Hypertension can be treated or untreatedBody mass index between 18.5 and 34.9 kg/m^2^

### Complete list of exclusion criteria

Secondary causes of hypertensionKnown target organ damagePharmacological BP treatment which has been initiated recently (< 1 month) and is still in the optimization phaseTen-year cardiovascular risk score > 5% according to the 2017 ACC/AHA guidelineClinically relevant metabolic, autoimmune, chronic, progressive, or malignant diseasesPostoperative phaseCurrent or chronic infectionsUse of antibiotics within 3 months before the studyRegular use of probiotics and dietary supplementsSpecial diet for medical reasonsFood intolerances and food allergiesVegan dietWeight loss diet or loss of more than 2 kg within 1 month before the studyInability to fully understand the significance, procedures, and scope of this studyKnown alcohol or drug abuseParticipation in another interventional study

The discontinuation criteria are withdrawal of consent, subsequent occurrence of an exclusion criterion (e.g., change of BP medication), lack of compliance, and other medical reasons for stopping the intervention.

An advantage in terms of compliance is the fact that patients only have to take a single dose of the probiotic or placebo for a relatively short period. A potential disadvantage is the fact that they only suffer from a mild form of hypertension, which might decrease compliance. To improve and/or ensure compliance, we ask patients before inclusion if they intend to be compliant, establish a good relationship, give simple and precise verbal and written instructions, and directly question patients for regular probiotics/placebo intake and estimate compliance by counting unused sachets. These efforts also improve the retention of patients in the study. In addition, we will detect probiotic bacterial strains in stool samples. However, these bacteria are thought to transiently colonize the intestine. Thus, their detection in stool samples after 8 weeks of intervention does not necessarily confirm rigorous compliance.

### Randomization

Eligible patients are included after the successful screening. Randomization is done by the supplier (see below) based on the lists generated with an ad hoc SAS® program (sex stratification, randomly varying block sizes). Based on these lists, the supplier delivers sequentially numbered boxes containing sachets to the study center without any information on group allocation. Thus, strictly concealed allocation and complete blinding are ensured. A person of trust from the study center not involved in the study has access to sealed envelopes for each participant, thereby enabling disclosure of group allocation if necessary.

### Probiotic intervention

Vivomixx® is a microbiotic food supplement. It contains eight strains of live bacteria (*Lactobacilli paracasei*, *plantarum*, *acidophilus*, and *delbrueckii*; *Bifidobacteria longum*, *infantis*, and *breve*; *Streptococcus thermophilus*) in a concentration of 450 billion bacteria per sachet. Patients take the content of two sachets dissolved in water in the evening (approx. every 24 h, either 30 min before or 2 h after dinner). Two sachets yield a daily dose of 9 × 10^11^ colony-forming units (CFU). The placebo group takes sachets with an identically appearing powder without any bacteria. Both interventional products are provided by the supplier Mendes S. A, Lugano, Switzerland.

### Adverse events

Vivomixx® has been safely used in other studies and was well tolerated, even in patients with irritable bowel syndrome [21]. Minor adverse events of probiotics can be increased gas, bloating, and stool frequency. These side effects are mild and transient. Nevertheless, we question all patients at each visit for related or unrelated health issues and record all adverse events. Serious adverse events due to this probiotic are not to be expected.

### Outcome parameters

All outcomes are assessed at three time points—at baseline, after 8 weeks of intervention, and 4 weeks after discontinuation (recovery).

Our primary hypothesis is that a probiotic containing eight different strains of live bacteria reduces BP in grade 1 hypertension. Accordingly, our primary endpoint is the mean nocturnal systolic BP after 8 weeks of probiotic intake compared to placebo and adjusted for the baseline value. We already used this outcome to attain a maximally standardized way of BP measurement [18]. Other established outcomes in hypertension research like office BP and ambulatory 24-h BP will be included as important secondary outcomes.

Further secondary endpoints are change of antihypertensive medication, fecal microbiome composition, fecal and serum metabolome, immune cell phenotypes, glucose variability after three standardized breakfasts and health-related quality of life from baseline.

We perform a 4-week follow-up after the intervention, in which procedures will be repeated to investigate any prolonged treatment effects. We will also control for BP-reducing lifestyle factors such as weight reduction (anthropometry) and dietary habits including salt intake (food records) before and after the intervention.

Body composition is measured by air-displacement plethysmography, and the blood is sampled for routine and research measurements as well as peripheral blood mononuclear cell (PBMC) isolation. In addition, patients rate their health-related quality of life with the PROMIS-29 questionnaire.

Glucose variability is measured by continuous glucose monitoring (FreeStyle Libre Pro, Abbott). For this, a sensor is placed in the adipose tissue (triceps region) where it measures the interstitial glucose concentration every 15 min for 7 days. To study possible changes in postprandial glucose concentrations, patients are asked to eat three standardized breakfasts on three consecutive mornings while wearing the sensor. These breakfasts are prepared in the study center and handed out to patients to eat at home. Breakfasts are similar in calorie and carbohydrate content but differ in glycemic index (high, medium, low).

To evaluate and control for dietary intake, patients record food and beverage consumption in 4-day food records while wearing the sensor. Although food records over the whole 7 days might have been preferable, 4-day records are considered to yield sufficient results, are less demanding on patients and investigators, and reduce the time in which dietary habits might change due to recording, e.g., undereating. Records will be analyzed for macro- and micronutrient content using OptiDiet Plus (V6.0, GOE, Linden, Germany). This professional analysis software uses the nutrient content of 12,000 foods provided by the German Nutrient Database.

From stool samples, bacterial DNA will be sequenced, and fecal and serum metabolites will be measured by mass spectrometry. We will explore metabolites with –omics-based methods. We hypothesize that changes in the gut microbiota affect the ratio of certain tryptophan metabolites and levels of short-chain fatty acids, which in turn affect immune responses and blood pressure. However, we will also design more experiments that address the biological question of this study. The obtained results will enable the construction of rigorous scientific hypotheses which can be tested later using -omic or non-omic methods.

Table 1 provides a detailed overview of assessments and endpoints.

**Table 1 Tab1:** Schedule of HYPRO study visits

Study visit	V0	V1	V2	V3
Time point	Screening	Baseline	Post-intervention	Recovery
Week	− 4 to − 1	0	8	12
Informed consent	x			
Inclusion/exclusion criteria	x			
Demographics	x			
Case history	x			
Medication	x	x	x	x
Physical exam	x			
Smoking status	x			
Height, weight, waist-to-hip ratio	x			
Blood pressure, heart rate, ECG	x			
Blood sample	x	x	x	x
Urine sample	x	x	x	x
AE/SAE query		x	x	x
Bodyweight and composition (ADP)		x	x	x
Office BP		x	x	x
24-h ABPM		x	x	x
PBMC isolation		x	x	x
Glucose sensor (7 days)		x	x	x
Food record (4 days)		x	x	x
Standardized breakfasts (3 days)		x	x	x
Stool sample		x	x	x
Health-related quality of life (PROMIS-29)		x	x	x

*ABPM* ambulatory blood pressure monitoring, *ADP* air-displacement plethysmography, *AE* adverse event, *BP* blood pressure, *ECG* electrocardiogram, *PBMC* peripheral blood mononuclear cells, *PROMIS* Patient-Reported Outcomes Measurement Information System, *SAE* serious adverse event

### Power calculation

Based on the above mentioned meta-analysis [9] and on our own unpublished data (NCT02509962, NCT02971787), we estimate a mean decrease in systolic BP of 3.8 mmHg with a standard deviation of 5.0 mmHg in the probiotic group. In addition, we assume that the placebo group will have the same systolic BP baseline value and a small decrease in the mean systolic BP of 0.2 mmHg with the same standard deviation. That leads to a standardized effect size between groups of (3.8 − 0.2)/(√2 × 5.0) ≈ 0.51. The required sample size to find a significant effect with a power of 0.8 at a two-sided significance level of 0.1 is given by 98 patients (49 per treatment arm, calculated with ADDPLAN, version 6.1). To account for approximately 10% dropout, the total number of patients to be recruited is 110 (98/110 ≈ 0.9).

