### Data analysis

A confirmatory analysis will be conducted based on the intention-to-treat (ITT) population, defined by the ITT principle. We want to show that the intervention group is superior to the control, i.e., the mean nocturnal systolic BP at 8 weeks after the start of treatment adjusted for the baseline value is lower in the intervention group than in the control group. An analysis of covariance (ANCOVA) adjusted for baseline systolic BP values using group allocation as a factor will be applied. The global two-sided significance level is 0.1. Missing values will be replaced using multiple imputation [22].

A sensitivity analysis to the primary efficacy ANCOVA model will be applied with additional covariates/factors given by age and sex. Subgroup analysis is planned for sex. Descriptive methods will be used for the analysis of all clinical, demographic, and safety parameters, including the calculation of appropriate summary measures of the empirical distribution as well as 95% confidence intervals and calculation of descriptive two-sided *p* values. A safety analysis of frequencies and rates of adverse events will be performed. Additionally, sensitivity analyses will be conducted for different populations (per-protocol population, patients with complete cases). Interim analyses are not included in our analysis plan. All analyses will be done using validated statistical software.

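### The power calculation divides the 3.6 mmHg difference by √2 × 5.0 although the stated SD is 5.0, so the effect size of 0.51 and the 80% power do not fit the stated inputs; the error is conservative

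*Protocol article*

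**What the plan says.** All the inputs stand in the Power calculation section of the protocol article. For the active arm: "we estimate a mean decrease in systolic BP of 3.8 mmHg with a standard deviation of 5.0 mmHg in the probiotic group". For placebo, from the same baseline value: "a small decrease in the mean systolic BP of 0.2 mmHg with the same standard deviation". The section continues "That leads to a standardized effect size between groups of" (3.8 − 0.2)/(√2 × 5.0), which it rounds to 0.51. It then gives the sample size "with a power of 0.8 at a two-sided significance level of 0.1 is given by 98 patients". This means 49 in each arm, obtained from the ADDPLAN software. The last step is the allowance for loss: "To account for approximately 10% dropout, the total number of patients to be recruited is 110".

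The section gives no correlation between baseline and week 8 and no reason for the √2. Under Data analysis, the primary test is fixed as follows: "An analysis of covariance (ANCOVA) adjusted for baseline systolic BP values using group allocation as a factor will be applied".

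**The concern.** The standardized effect for two independent groups is the difference in means divided by the common within-group SD. The fact that two means are being compared is already covered by the factor 2 in the sample-size formula. A further √2 in the denominator of the effect size halves the squared effect and so doubles the required number.

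The article prints the inputs, the formula and the result together, and the result does not follow from the inputs. Two things are at stake. The stated power does not describe the trial that the stated assumptions imply. The planning SD is also left ambiguous between 5.0 and about 7.1 mmHg, and that matters for reading a null result: under the first value the trial had about 97% power to detect 3.6 mmHg, under the second about 80%.

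**Working it through.** **Inputs** (all from Power calculation, except the analysis model, which is from Data analysis): decreases of 3.8 and 0.2 mmHg, so a difference of 3.6; SD 5.0 in each arm; two-sided level 0.10; power 0.80; 49 per arm; baseline-adjusted ANCOVA.

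**Formula.** The normal approximation for the number per arm is n = 2(z₀.₉₅ + z₀.₈₀)²/d², with (1.645 + 0.842)² ≈ 6.18. The exact figures below use the noncentral t distribution with noncentrality d·√(n/2).

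**Step 1: reproduce the article's figure.**
- d = 3.6/(√2 × 5.0) = 3.6/7.071 = 0.509.
- Normal approximation: 2 × 6.18/0.509² ≈ 47.7, so 48 per arm.
- Noncentral t: 48.4, so 49 per arm and 98 in total, with power 0.804. This is the article's figure.
- Dropout: 98/0.9 = 108.9, so 109; the stated 110 is within rounding.

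**Step 2: use the SD as stated.**
- d = 3.6/5.0 = 0.72.
- Normal approximation: 2 × 6.18/0.72² ≈ 23.8, so 24 per arm.
- Noncentral t: 24.6, so 25 per arm and 50 in total. With 10% dropout, 50/0.9 = 55.6, so 56.
- At 49 per arm the power is 0.971 at two-sided 0.10 and 0.942 at two-sided 0.05.
- Put the other way, 49 per arm gives 80% power at two-sided 0.10 for a difference of about 2.5 mmHg when the SD is 5.0.

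| SD used | d | Per arm for 80%, two-sided 0.10 | Per arm for 80%, two-sided 0.05 | Power at 49 per arm, two-sided 0.10 |
|---|---|---|---|---|
| 7.07 | 0.51 | 49 | 62 | 80% |
| 5.0 | 0.72 | 25 | 32 | 97% |

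**Step 3: does the planned ANCOVA change this?** Let ρ be the correlation between baseline and week 8, with equal variance at both visits.
- If 5.0 is the SD of the change, the ANCOVA residual SD is 5.0·√((1 + ρ)/2), which is at most 5.0.
- If 5.0 is the SD at a single visit, the residual SD is 5.0·√(1 − ρ²), again at most 5.0. At ρ = 0 it is 5.0 (25 per arm), at ρ = 0.5 it is 4.33 (19 per arm), and at ρ = 0.7 it is 3.57 (13 per arm).

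On either reading d is at least 0.72 for the test that will be used.

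**Step 4: other conventions.** With SD 5.0, two-sided levels of 0.10 and 0.05 and one-sided levels of 0.10, 0.05 and 0.025 need between 18 and 32 per arm. Two-sided 0.025 needs 38. None reaches 49.

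**Step 5: sensitivity to the SD.** The SDs of 6, 8 and 10 are assumptions of this review, not values from the article. At 49 per arm and two-sided 0.10, SD 6 gives 90%, SD 7.07 gives 80%, SD 8 gives 71% and SD 10 gives 55%.

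**The case against.** The best defence is that √2 × 5.0 is exactly the SD of a change score when 5.0 is the SD at each visit and baseline and week 8 are uncorrelated. The remark that both arms share the same baseline value could point to such a before-and-after calculation. This is a possible origin of the √2, so it cannot be stated as fact that the factor was counted twice by mistake. It does not rescue the figure, however. The text attaches 5.0 to the decrease and states no correlation. Under this reading the planned ANCOVA would still have a residual SD of at most 5.0.

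It is also fair to say that 98 does follow from 0.51. The effect size, power and sample size are not three separate errors; one wrong effect size carries through to the other two.

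The direction is conservative, the study is described as exploratory, and the endpoint, model, significance level and analysis population are all untouched. That stands, and it limits how serious the point is.

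A reader might infer that the 0.10 level was adopted because the understated effect size made 0.05 look unaffordable (62 per arm rather than 49). The article does not support that. It gives no reason for 0.10, and the exploratory design is an equally available explanation. All that can be said is that, on the stated inputs, 49 per arm would give about 94% power at two-sided 0.05.

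**Conclusion.** The point holds, confined to the effect size. With a difference of 3.6 mmHg and a common SD of 5.0, the standardized effect is 0.72, not 0.51. The number needed for 80% power at two-sided 0.10 is 25 per arm, not 49, and the power at 49 per arm is about 97%, not 80%. The stated 80% arises only with a between-patient SD of about 7.1 mmHg, which the article nowhere states.

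These figures rest on the article's own difference and SD, a two-sample comparison with equal arms, and 98 evaluable patients. Baseline adjustment can only raise the power further.

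A reader might take a faulty power calculation to mean an underpowered trial. On the stated assumptions the opposite is true: the trial is larger than they require. Whether 5.0 is the right SD for nocturnal systolic BP cannot be judged from this document, because the sources behind it are not shown. The paragraph should be fixed, but the error does not threaten the validity of the primary analysis.

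**What to change.** Keep 110 patients and rewrite the paragraph. State the effect size as 3.6/5.0 = 0.72, the power as about 97% at two-sided 0.10 with 98 evaluable patients, and say that 5.0 mmHg is the SD of the change in systolic BP.

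Only if a between-patient SD of about 7.1 mmHg was really the planning assumption should the paragraph take the other route. It should then state that SD, give its source, say which single quantity it describes (the change or the ANCOVA residual), and remove the 5.0. Without a source, this would fit the SD to a sample size already chosen, after recruitment had begun.

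The cost is one corrected paragraph. Patient numbers, procedures and the analysis do not change.
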